#### Resistance Marker Study

The primary outcome is the prevalence of relevant SP+AQ– and piperaquine-associated antimalarial resistance phenotypes: *P falciparum* dihydrofolate reductase gene (*Pfdhfr*)—codons 51, 59, 108, and 164; *P*
*falciparum* dihydropteorate synthetase gene (*Pfdhps*)—codons 431, 437, 540, 581, and 613; *P*
*falciparum* chloroquine resistance transporter gene (*Pfcrt*)—codons 72 to 76; and *P*
*falciparum* multidrug resistance gene 1 (*Pfmdr1*)—codons 86, 184, and 1246.

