### Objectives

Phase 2 aims to test the feasibility, effectiveness, and chemoprevention efficacy of SMC with SP plus AQ (SP+AQ) in Nampula Province in Mozambique, where malaria transmission is highly seasonal. Specific objectives include the following:

To determine the effectiveness of SMC in reducing the incidence of malaria infection among children aged 3 to 59 months.To determine and measure efficacy as follows:To determine chemoprevention efficacy of SP+AQ when used for SMC in Nampula Province, Mozambique.To calculate the extent to which efficacy is impacted by drug resistance and drug concentrations.To investigate the presence and change of SP+AQ– and piperaquine-resistance markers over time as a result of SMC implementation.To understand the impact of the SMC implementation model by determining process, costing, and acceptability outcomes for the intervention.

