#### Resistance Marker Study

The sample size for the survey was determined using a sample size calculation from a WHO protocol for drug efficacy testing [29], with the intention to estimate changes in prevalence of SP- and AQ-resistance markers with enough precision to provide adequate power to detect changes if they occur. A sample of 300 children per district—150 each at baseline and end line—is expected to result in 90% power to detect a difference at the 5% confidence level in sextuple SP mutants from less than 1% to 2%. In Lalaua, where the chemoprevention efficacy study will be conducted, we determined that a sample of 600 children—300 each at baseline and end line—is needed to obtain a sufficiently accurate specific prevalence measure in the absence of data on malaria parasite ecologies. This will result in a total sample size across both districts of 1500, with 750 children sampled at both baseline and end line.

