#### Resistance Marker Study

Prevalence of *Pfdhps*, *Pfdhfr,*
*Pfcrt*, and *Pfmdr1* alleles in parasites obtained from participating children will be ascertained. Copy numbers of *Pfplm2* will also be quantified.

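### The resistance marker study is sized on a change in sextuple SP mutants that its primary outcome and analysis do not name, and the 90% power stated for that change is not delivered

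*Protocol article*

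**What the plan says.** All references are to the Protocol article.

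- **Objectives.** The third objective is "To investigate the presence and change of SP+AQ– and piperaquine-resistance markers over time as a result of SMC implementation".
- **Primary and Secondary Outcomes, Resistance Marker Study.** "The primary outcome is the prevalence of relevant SP+AQ– and piperaquine-associated antimalarial resistance phenotypes". The list that follows covers *Pfdhfr* ("codons 51, 59, 108, and 164"), *Pfdhps* ("codons 431, 437, 540, 581, and 613"), *Pfcrt* ("codons 72 to 76") and three *Pfmdr1* codons. No marker or combination is singled out, and *Pfplm2* is absent.
- **Sample Sizes, Resistance Marker Study.** "A sample of 300 children per district—150 each at baseline and end line" is expected to give "90% power to detect a difference at the 5% confidence level in sextuple SP mutants from less than 1% to 2" percent. Lalaua has 300 at each time point instead of 150, and the total is 1500.
- **Recruitment and Data Collection, Resistance Marker Study.** Samples come from four health facilities in each of the four districts. The same codons are listed, with *Pfplm2* added for the two new districts to inform later studies.
- **Data Analysis, Resistance Marker Study.** Prevalence of *Pfdhps*, *Pfdhfr*, *Pfcrt* and *Pfmdr1* "alleles in parasites obtained from participating children will be ascertained", and *Pfplm2* copy number is quantified. Sextuple mutants are not mentioned.

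**The concern.** The outcome, sample size and analysis sections should describe the same quantity, and here they do not. An analyst following the outcome section would report a table of codon prevalences. One following the sample size section would report a before-after comparison of a multi-codon haplotype. Both could claim to have done the primary analysis.

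The power figure makes this worse. A reader who believes that each district had 90% power will take a non-significant result as evidence that SMC did not raise sextuple mutant prevalence. If the true power is nearer 10% to 30%, such a result says very little. This component is meant to show whether SMC changes resistance, so false reassurance is the main risk.

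**Working it through.** **1. Outcome against sizing endpoint.** The outcome list holds 4 *Pfdhfr* + 5 *Pfdhps* + 3 *Pfmdr1* codons, plus *Pfcrt* 72 to 76. That is 13 markers if *Pfcrt* is one haplotype, or 17 by codon. A sextuple SP mutant would presumably combine codons from the two SP genes, but the article does not say which six. Separate codon prevalences do not determine a joint one: two alleles each at 50% can occur together in anything from 0% to 50% of infections.

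**2. Sample totals.** Three districts at 300 plus Lalaua at 600 gives 3 × 300 + 600 = 1500. Per time point it is 3 × 150 + 300 = 750. Both match the article and fit four districts, so its reference to both districts beside this total is a slip.

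**3. The stated 90% power.** Inputs from the article: n = 150 per time point, end-line prevalence 2%, 5% level. It gives the baseline only as below 1% and does not state sidedness. I assume a two-sided test and show baselines from 0% to 1%.

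Power is the sum, over all pairs of counts (i, j) with Pearson p ≤ 0.05, of Bin(i; n, p1) × Bin(j; n, p2).

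| Baseline p1 | 150 vs 150 | 300 vs 300 (Lalaua) | 750 vs 750 (all districts) |
|---|---|---|---|
| 1% | 9.3% | 15.8% | 36.3% |
| 0.5% | 17.9% | 37.1% | 77.7% |
| 0.1% | 30.8% | 72.4% | 98.7% |
| 0% | 35.3% | 85.1% | about 100% |

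The 0% entry at n = 150 can be checked by hand.
- At 2%, 150 × 0.02 = 3 mutants are expected at end line.
- With none at baseline, 3 vs 0 gives z = 0.0200 / √(0.0100 × 0.9900 × 2/150) = 1.74, not significant.
- 4 vs 0 gives z = 0.0267 / √(0.0133 × 0.9867 × 2/150) = 2.01, significant.
- Power is therefore P(X ≥ 4) for X ~ Bin(150, 0.02) = 1 − (0.0483 + 0.1479 + 0.2248 + 0.2263) = 0.353.

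Other methods at 150 vs 150:
- Normal approximation, two-sided: 10.6% from 1%, 21.4% from 0.5%, 36.4% from 0.1%.
- Fisher's exact test: at most 8.2%, even from 0%.
- Arcsine approximation from exactly 0%: 69% two-sided, 79% one-sided.
- Chance of seeing at least one mutant at 2%: 1 − 0.98^150 = 95%. This is a detection probability, not power for a difference.

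None gives 90%. The arcsine method from 0% passes 90% (93.5%, two-sided) only with 300 per time point, which is Lalaua's size.

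**4. Size needed for 90% power.** n = [1.96 √(2p̄(1 − p̄)) + 1.2816 √(p1(1 − p1) + p2(1 − p2))]² / (p2 − p1)², with p̄ = (p1 + p2)/2. From 1% to 2%: (0.3369 + 0.2201)² / 0.0001 ≈ 3103 per time point. From 0.5% the result is 1151, and from 0.1% it is 603.

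**5. Effect of facility clustering on the combined contrast.** The article gives no design effect. As an illustration, a design effect of 1.25 leaves 750 / 1.25 = 600 effective children per time point. By the normal approximation, power then falls from 35.7% to 29.6% (baseline 1%), from 74.4% to 64.8% (0.5%) and from 95.1% to 89.9% (0.1%).

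**The case against.** The best defence is that this is a condensed article about a descriptive component. Study Design speaks of describing changes in marker prevalence, and Data Analysis plans estimation only. A full protocol or SAP may define the haplotype, rank the markers and set out any multiplicity control. The SP-gene codons needed to build an SP haplotype are probably in the list. This defence stands as far as ranking and alpha control go, and their absence is not held against the plan. It does not remove a mismatch between sections of the current text, nor a power figure that fails on its own inputs.

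Two stronger readings are tempting and are not supported.

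- **That the study has no primary contrast.** The sample size section does state one: baseline versus end line, sextuple mutants, per district, 5% level. The fault is that it is undefined and not tied to the outcome or the analysis.
- **That a chance change is likely.** Testing 13 markers in 4 districts, 52 independent tests at 5%, would give 1 − 0.95^52 = 93% chance of at least one false change. With a within-district correlation of 0.5 it would be 80%. The article does not plan those tests, and rare or near-fixed alleles have true test sizes well below 5%. For the one contrast it names, tested in each of the four districts, the chance of any false change by Pearson test is 12.8% at 1% prevalence, 4.9% at 0.5% and below 0.1% at 0.1%. The risk arises only if the listed markers are tested one by one at 5% without correction.

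A fair point against the repair is that combining districts mixes Malema and Mecubúri, exposed in phase 1, with Lalaua and Muecate, which are new to SMC.

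**Conclusion.** The concern holds as a mismatch and a wrong power figure. The endpoint that sizes the study is neither defined, nor listed as the primary outcome, nor analysed. Its per-district power is about 9% to 31% for baselines of 1% to 0.1%, and at most 35% from 0% by two-sided Pearson test, against the 90% stated. The omission of *Pfplm2* from an outcome that claims piperaquine-associated markers is a smaller inconsistency of the same kind.

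The figures assume independent children, one usable genotype per child and a two-sided 5% test. The baselines are assumptions within the article's bound of below 1%. Clustering by facility would generally lower the power. The figures for 750 versus 750 come from a simple two-sample test. A district-stratified test should be close to them, because every district has equal numbers at the two time points.

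The point should be corrected, but it concerns this component only and not the cluster randomized trial.

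**What to change.** 1. Define the sextuple SP haplotype by its codons, and say how mixed infections are classified.
2. In both the outcome and analysis sections, name one primary contrast: the end-line versus baseline change in that haplotype's prevalence across all four districts. Use a two-sided 5% test stratified by district (Mantel-Haenszel, or a logistic model with district), allowing for sampling through four facilities per district.
3. Report single codons, per-district results and *Pfplm2* descriptively with 95% CIs and no significance claims. State in the outcome section that *Pfplm2* is the piperaquine marker and belongs to this set.
4. Replace the 90% statement with the power of the combined contrast: about 36% from 1%, 78% from 0.5% and 99% from 0.1% to 2%, before facility clustering. Give the assumed baseline, and correct the reference to both districts.

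The cost is wording and one analysis of samples already planned. The Results section says collection ended in mid-June 2022, so the contrast should be fixed before baseline and end-line genotypes are compared. If they have been compared already, the report should say so. The price is that a change confined to one district, or a difference between phase 1 and new districts, is reported with its interval and not as a test result. Even combined, power stays low if the baseline is close to 1%, and the report should say that too.

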### Sample Sizes

#### Cluster Randomized Controlled Trial

Clusters will be selected for the intervention arm at the community level in two districts. The study will be powered to have an 80% chance of detecting a significant reduction in RDT-confirmed malaria incidence at the 5% confidence level using a chi-square test comparing two independent proportions in a cluster randomized design. We are aiming to detect a significant reduction in malaria incidence from 0.2 to 0.12 clinical episodes per child per high-transmission season, corresponding to the SMC round. The clinical episodes should be of sufficient severity to present to a health facility, and the reduction in episodes should be equivalent to an odds ratio of 0.66, or a minimum effect size of 33%. This is based on the assumption that the efficacy of SP+AQ in Northern Mozambique, where the prevalence of resistance alleles in circulating parasites is high, is half of that found in studies in West African settings. To account for the cluster randomized design, we assumed an intracluster correlation for malaria outcomes within communities of 0.23, based on data from SMC coverage surveys conducted by the Malaria Consortium in 2020 [27] and 2021 [28]. A cluster size of 15 children per community was selected, and children in the intervention and control arms were recruited in a ratio of 1:1.5. This resulted in a total sample size of 2850 eligible children in 190 clusters: 1710 in 114 clusters in the control arm and 1140 in 76 clusters in the intervention arm. A total of 76 communities from a list of all communities will be selected as intervention districts using a simple random method. Then, 114 communities will be selected at random from among those remaining for inclusion in the control arm.

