## Introduction

### Overview

The World Health Organization (WHO) defines seasonal malaria chemoprevention (SMC) as the intermittent administration of full treatment courses of an antimalarial medicine during the malaria season to prevent malarial illness, with the objective of maintaining therapeutic antimalarial drug concentrations in the blood throughout the period of greatest malarial risk [1-5]. It involves administering monthly courses of sulfadoxine-pyrimethamine (SP) and amodiaquine (AQ) during this peak transmission period to those most at risk: children 3 to 59 months of age [6]. SMC has been demonstrated to be a highly effective intervention that can prevent up to 75% of malaria cases in eligible children [7]. It has also been shown that the intervention can be delivered safely at scale, achieving high coverage [8,9]. To date, SMC has only been adopted and scaled up in Sahelian countries of West and Central Africa, following the WHO recommendation for this region to be the first to implement SMC. However, in many parts of East and Southern Africa, there remain concerns over widespread resistance to SP, which may reduce the effectiveness of SMC [10,11]. However, it has been suggested that SP may retain its protective efficacy even in areas where resistance is high [12,13].

Mozambique accounts for 4% of global malaria cases, and the disease is highly endemic in the entire country, with the highest prevalence in the north and along the coast [14-16]. According to surveys conducted in Mozambique, the national prevalence of malaria in children aged 6 to 59 months remained stable at 38% in 2011 [17], 40% in 2015 [18], and 39% in 2018 [19]. The prevalence varies across the country, with it being higher in the northern and central provinces and lower in the southern provinces. Nampula was one of the provinces with the highest prevalence of malaria (65%-66%) in 2015. However, a slight decrease was observed in 2018 to 48%, but it remained one of the highest prevalence rates after Cabo-Delgado (57%) [19]. Among chemoprevention strategies implemented in Mozambique, for more than 10 years, the Mozambique Ministry of Health and the National Malaria Control Programme (NMCP) have been actively implementing intermittent preventive treatment in pregnancy using SP [18].

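### The cluster trial's target effect is given as 0.20 to 0.12, odds ratio 0.66 and 33%, which disagree; 80% power holds only for 0.20 to 0.12 and falls to about 50–63% at the stated minimum

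*Protocol article*

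**What the plan says.** All the design inputs are in the Protocol article, Sample Sizes, Cluster Randomized Controlled Trial.

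- Power: "The study will be powered to have an 80% chance of detecting a significant reduction in RDT-confirmed malaria incidence".
- Test: "at the 5% confidence level using a chi-square test comparing two independent proportions in a cluster randomized design".
- Target: "We are aiming to detect a significant reduction in malaria incidence from 0.2 to 0.12 clinical episodes per child per high-transmission season".
- The same target re-expressed: "the reduction in episodes should be equivalent to an odds ratio of 0.66, or a minimum effect size of 33"%.
- Rationale: efficacy in Northern Mozambique "is half of that found in studies in West African settings".
- Clustering: "we assumed an intracluster correlation for malaria outcomes within communities of 0.23", with 15 children per community.
- Size: 1710 children in 114 control clusters and 1140 in 76 intervention clusters, 2850 in 190 in all.

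The paragraph gives no separate calculation for the odds ratio or the percentage. It presents them as the same effect as the fall from 0.2 to 0.12.

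**The concern.** The three descriptions cannot all be the same effect. Moving from 0.20 to 0.12 removes two fifths of cases, and its odds ratio is well below 0.66. Because the smaller effect is labelled the minimum, a reader will take it that the trial has 80% power there.

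This affects interpretation. The minimum effect is justified by high resistance to sulfadoxine-pyrimethamine, which is the trial's policy question. If power at that effect is nearer one half than four fifths, a non-significant result says much less about whether chemoprevention fails in such an area than the stated power suggests.

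A secondary point is that 0.2 and 0.12 are given as episodes per child, which are rates, while the calculation is for proportions.

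**Working it through.** **Inputs** (all from the sample-size paragraph): control risk 0.20; 15 children per cluster; intracluster correlation 0.23; 1710 control and 1140 intervention children; 5% level. Sidedness is not stated, so two-sided is taken as the base case.

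**Step 1. Are the effects equivalent?**

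- 0.20 to 0.12: risk ratio 0.12/0.20 = 0.60, a 40% reduction. Odds ratio (0.12/0.88)/(0.20/0.80) = 0.545.
- Odds ratio 0.66 from 0.20: odds 0.66 × 0.25 = 0.165, risk 0.165/1.165 = 0.1416. Reduction 1 − 0.1416/0.20 = 29.2%.
- 33% reduction from 0.20: 0.20 × 0.67 = 0.134. Odds ratio (0.134/0.866)/0.25 = 0.619.

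**Step 2. Effective sample sizes.** Design effect = 1 + (15 − 1) × 0.23 = 4.22. Control 1710/4.22 = 405.2; intervention 1140/4.22 = 270.1.

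**Step 3. Reproduce the plan's figure with 0.20 against 0.12.**

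- Pooled risk = 0.6 × 0.20 + 0.4 × 0.12 = 0.168.
- Standard error under no difference = √[0.168 × 0.832 × (1/405.2 + 1/270.1)] = 0.0294.
- Standard error under the alternative = √[0.20 × 0.80/405.2 + 0.12 × 0.88/270.1] = 0.0280.
- Power with pooled variance = Φ[(0.08 − 1.96 × 0.0294)/0.0280] = Φ(0.80) = 79%.
- Power with unpooled variance = Φ(0.08/0.0280 − 1.96) = Φ(0.89) = 81%.

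Solving for total size at 80% power gives 2933 children (pooled) or 2746 (unpooled). These bracket the stated 2850, so the plan's number comes from 0.20 against 0.12.

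**Step 4. The same calculation for the other stated effects.**

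| Effect from 0.20 | Intervention risk | Power, pooled | Power, unpooled | Children for 80% power |
|---|---|---|---|---|
| 40% reduction, odds ratio 0.545 | 0.120 | 79% | 81% | 2746–2933 |
| 33% reduction, odds ratio 0.62 | 0.134 | 61% | 63% | about 4230–4450 |
| Odds ratio 0.66, 29% reduction | 0.1416 | 50% | 52% | about 5550–5790 |

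The last row is about 370 clusters (5550/15) to 386 (5790/15), against 190. With 2850 children and pooled variance, the smallest effect that reaches 80% power is about 0.20 to 0.119, a 40.5% reduction.

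**Step 5. Does another reading reconcile the figures?**

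- *33% meaning one minus the odds ratio.* 1 − 0.66 = 34%, so these two then nearly agree with each other. Both still contradict 0.20 to 0.12 (odds ratio 0.545), and power is about 50%.
- *One-sided test.* Pooled power is 87% for 0.12, which does not match the plan, and 72% and 62% for the two smaller effects, still below 80%.
- *Intervention risk fixed at 0.12 and the control risk lowered.* Pooled power is 55% (33% reduction) and 44% (odds ratio 0.66).
- *0.2 and 0.12 as Poisson rates (an assumption, not in the article).* Risks of at least one case are 1 − e^(−0.20) = 0.181 and 1 − e^(−0.12) = 0.113: odds ratio 0.576, 38% reduction. This matches neither figure, and power is 68–71% even for the largest effect.

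**The case against.** The strongest case on the other side is that the sizing is correct and only its translation is wrong. The 80% claim is followed directly by the 0.2 to 0.12 target, and 2850 children fits that target. The article never separately claims power for an odds ratio of 0.66. That is fair, but calling the effects equivalent and the smaller one a minimum leads a reader to infer 80% power there, and that inference is false.

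Other points stand in part:

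- The odds ratio and the 33% may be one figure rather than two, if the percentage is one minus the odds ratio. There is then one contradiction instead of two, and the relevant power is the lower one, about 50%.
- The halving rationale does not settle the matter, but it is not a clear contradiction either. The Introduction says the intervention "can prevent up to 75% of malaria cases in eligible children", and half of that is 37.5% (0.125, power 73–76%). That is an upper figure, however, and the sample-size paragraph does not say it was the one halved.
- The rate wording may be loose. The Data Analysis section tests the proportion of children with one or more confirmed cases, which fits a calculation on proportions. The Poisson result is a sensitivity figure only.
- The loss of power matters only if the true effect is near the minimum. A 50% reduction would have about 95% power. The Discussion reports 86% lower odds in phase 1, an effect that would have power above 99.9%, but that comparison was not randomized.
- The Cox models may have somewhat different power, but the article rests its claim on the chi-square test.
- Data collection ended in mid-June 2022, so the sample size cannot change. The point concerns reporting and interpretation.

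**Conclusion.** The concern holds. The target effects called equivalent are not, and no plausible reading makes them so. The 190 clusters give 80% power for a fall from 0.20 to 0.12 only. At the stated minimum effect, power is 61–63% if 33% is a risk reduction and 50–52% if the odds ratio of 0.66 is meant, so the chance of missing such an effect is roughly 37–50% rather than 20%.

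These figures assume a two-sided 5% test, a control risk of 0.20, and the article's own intracluster correlation and cluster size. The risk of misreading a null result arises only if the true effect lies near the minimum. The half-of-75% and Poisson figures rest on assumptions and are not needed for the conclusion. The power claim should be corrected because it concerns the primary comparison and is wrong as written.

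**What to change.** Keep the 190 clusters and state one effect, on one scale, with the power that belongs to it. The simplest correction is: 80% power, two-sided 5%, to detect a fall from 20% to 12% of children with at least one RDT-confirmed case during the season (risk ratio 0.60, odds ratio 0.55, a 40% reduction). Remove the odds ratio of 0.66 and the 33%, and say that the inputs are proportions, not episode rates.

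If the smaller effect is what the investigators regard as the minimum of interest, they should choose one of its two forms and give its power: about 61–63% for a 33% risk reduction, or about 50–52% for an odds ratio of 0.66.

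In either case, a non-significant result should be read from the confidence interval: whether it excludes the minimum effect, not merely whether p exceeds 0.05.

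The cost is one reworded paragraph and, if the smaller effect is kept, a less favourable stated power. No further children or clusters are needed.
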